### Study design and outcomes

#### Outcomes

The first endpoint variable is the rate of food intolerance in preterm children. The second endpoint variables include (1) time to achieve full enteral nutrition; (2) time of parenteral nutrition; (3) time of NICU stay; (4) meconium drainage time; (5) daily spontaneous fecal discharge conditions; (6) growth and development conditions during the NICU stay and within 3 months after discharge, including daily weight growth rate, weekly body length growth rate and weekly head circumference growth rate; (7) different plasma parameter indicators before discharge from the NICU (total protein (TP), albumin, calcium (Ca), phosphorus (P), and alkaline phosphatase (ALP)). Other endpoint variables include the incidences of neonatal necrotizing enterocolitis, cholestasis, parenteral nutrition-associated cholestasis and congenital hypothyroidism (CH).

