#### Introduction to the formulae

The two kinds of formula for feeding during the NICU stay and the formula for feeding after discharge from the NICU are all Dumex, a brand of French Danone-Nutricia for early life nutrition. In this study, the gestational age of all preterm children when discharged from the NICU is all ≥34 weeks, and thus formula suitable for 0 to 6-month-old infants is uniformly chosen for them after discharge. The ingredients of such formulae are shown in Table 1.

**Table 1 Tab1:** Table of ingredients of the three formulae

Ingredients	Preterm children’s formula (/100 ml)	Extensively hydrolyzed formula (/100 ml)	Formula for 0 to 6-month-old infants (/100 ml)
Energy (kcal/KJ)	80/336	66/278	67/282
Osmolality (mOsmol/L)	360	250	-
Fat (g)	3.8	3.5	3.5
α-linolenic acid (mg)	44	58	42
Linoleic acid (g)	0.6	0.41	0.42
Oleic acid (g)	1.3	1.2	-
Medium-chain triglyceride content (%)	30 %	40 %	-
Protein (g)	2.6 (60 % whey protein and 40 % casein)	1.6 (100 % whey protein)	1.4
Carbohydrates	8.4	6.9	7.1
Lactose (g)	5.6	2.8	-
Prebiotics (galactooligosaccharides, polyfructose) (g)	0.8	0.8	0.8
Arachidonic acid (mg)	19	6.6	12
Docosahexaenoic acid (mg)	15	6.6	12
Taurine (mg)	5.5	5.3	5.4
L-carnitine (mg)	1.8	1	1.5
Nucleotides (mg)	3.4	3.2	3.0
Vitamin A (μg)	359	52	65
Vitamin D (μg)	3	1.3	0.95
Vitamin E (mg)	3.5	1	1.2
Vitamin K1 (μg)	6	4.7	5.4
Vitamin B1 (μg)	139	50	58
Vitamin B2 (μg)	199	99	103
Vitamin B6 (μg)	119	40	48
Vitamin B12 (μg)	0.24	0.18	0.31
Nicotinamide acid (μg)	2352	432	517
Folic acid (μg)	35	9	11
Pantothenic acid (μg)	876	327	354
Vitamin C (mg)	17	9	9.2
Biotin (μg)	3.5	2.2	2.3
Choline (mg)	17	10	16
Inositol (mg)	24	3.2	3.8
Sodium (mg)	70	20	20
Potassium (mg)	80	75	69
Copper (μg)	80	40	48
Magnesium (mg)	8	5.1	5.7
Iron (mg)	1.6	0.53	0.71
Zinc (mg)	1.1	0.5	0.5
Manganese (μg)	10	7.4	7.5
Calcium (mg)	100	47	52
Phosphorus (mg)	56	26	31
Iodine (μg)	25	12	11
Chlorine (mg)	85	41	48
Selenium (μg)	4.5	1.5	2.2

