Incidence and outcome of feeding intolerance in preterm children, neonatal necrotizing enterocolitis, cholestasis, parenteral nutrition-associated cholestasis and congenital hypothyroidism3.Collection of enteral and parenteral nutrition and defecation conditions during the NICU stay:Milk opening time (h), total amount of daily milk (ml) and calories (kcal), total amount of daily parenteral nutrition (ml) and calories (kcal), total volume of daily fluids (ml) and total calories (kcal)The number of daily bowel movements, times of daily enema, trait and color of stool every time, meconium drainage time (h)Gastric residual volume (ml) and nature, times and nature of vomiting, and abdominal distensionTime to achieve full enteral nutrition (d), and total time of parenteral nutrition4.Collection of physical growth and development indicators during the NICU stay:Weight: weight will be measured at admission, once every day during hospital stay and before discharge with a baby electronic scale, and the data will be accurate to 10 g.Body length: body length will be measured at admission, once every week during hospital stay and before discharge, and the data will be accurate to 0.1 cm.Head circumference: head circumference will be measured at admission, once every week during hospital stay and before discharge, and the data will be accurate to 0.1 cm.5.Collection of laboratory indicators during the NICU stay:Daily monitoring of peripheral blood glucose and transcutaneous bilirubinWeekly detection of blood, liver and kidney function (total protein, albumin, total bilirubin, direct bilirubin, alkaline phosphatase, bile acids, alanine aminotransferase, aspartate aminotransferase, γ-glutamyl transferase, urea nitrogen, creatinine) and electrolytes (mainly calcium and phosphorus)Test of serum thyroid function 1–2 weeks after admission, including TSH, TT_3_, TT_4_, FT_3_ and FT_4_

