#### Secondary outcome

The time to reach enteral nutrition (parenteral nutrition), length of hospital stay, meconium drainage time during the NICU stay will be summarized and compared using Kaplan-Meier estimators and logrank tests. Cox models will also be fitted for time-to-event data adjusting for baseline covariates. The number of times of self-defecating per day will be compared using the Poisson model adjusting for baseline covariates. The rates of comorbidity will be compared using Poisson models. The plasma total protein, albumin level, calcium, alkaline phosphatase levels before discharge from the NICU will be compared using *t* tests. Growth rates measure by weight, body length, and head circumference during the NICU and within 3 months of discharge will be analyzed using repeated measurement analysis of covariance models. All analysis will be conducted using SAS 9.4 (SAS Institute, Cary, NC, USA).

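### Phosphorus is a listed and measured plasma endpoint but has no stated analysis, and the other four plasma markers get t tests that leave collected baseline covariates unused

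*Protocol article*

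**What the plan says.** - **Endpoint list (Outcomes).** Secondary endpoint 7 is "different plasma parameter indicators before discharge from the NICU (total protein (TP), albumin, calcium (Ca), phosphorus (P), and alkaline phosphatase (ALP"), which makes five markers.
- **Data collection (Collection of clinical data during the NICU stay).** The weekly laboratory panel includes liver function tests and "electrolytes (mainly calcium and phosphorus"). Gestational age and birth weight are among the general data recorded for every infant.
- **Analysis (Secondary outcome).** "The plasma total protein, albumin level, calcium, alkaline phosphatase levels before discharge from the NICU will be compared using" t tests. Phosphorus is not named, and no covariates are given.
- **Other analyses in the same paragraph.** "Cox models will also be fitted for time-to-event data adjusting for baseline covariates"; the stool-count Poisson model is also adjusted for baseline covariates, and growth is assigned a repeated-measures analysis of covariance.
- **Formula composition (Table 1; columns are preterm formula, EHF, 0 to 6-month formula, per 100 ml).** "Phosphorus (mg) 56 26 31" and "Calcium (mg) 100 47 52".
- **Timing of the sample.** It is fixed by an event, NICU discharge. "3) time of NICU stay" is itself a secondary endpoint, and the secondary objective asks whether EHF shortens it.

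**The concern.** The endpoint list and the analysis list disagree within the same article. A secondary endpoint without a stated analysis leaves the analyst free to decide afterwards whether and how to report it. Here the marker is relevant: the secondary objective asks whether EHF meets nutritional needs, and EHF supplies roughly half as much phosphorus per unit volume as the comparator.

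The second part concerns efficiency and consistency. The plasma markers are measured repeatedly, and two baseline variables that plausibly predict them are on file. Even so, they get a single-time comparison with no stated adjustment, while neighbouring outcomes are adjusted. Precision is lost at no saving.

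The third part concerns interpretation. Because the sample is taken before discharge, and the formula may shift discharge, a difference in values could reflect the formula itself, a different age at sampling, or both.

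**Working it through.** The plan gives no figure for these markers, so there is none to reproduce. The check compares the lists, takes ratios from Table 1, and adds two illustrations.

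**1. Lists side by side**

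| Marker | Endpoint list (Outcomes) | Collected weekly | Analysis stated |
|---|---|---|---|
| Total protein | yes | yes | t test |
| Albumin | yes | yes | t test |
| Calcium | yes | yes | t test |
| Phosphorus | yes | yes | none |
| Alkaline phosphatase | yes | yes | t test |

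Five are listed, four are analysed, and phosphorus is the one missing.

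**2. Formula difference (Table 1, per 100 ml)**

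- Phosphorus: 26/56 = 0.464, or 54 % lower in EHF.
- Calcium: 47/100 = 0.470, or 53 % lower.
- Other minerals: sodium 20/70 = 0.29, iron 0.53/1.6 = 0.33, selenium 1.5/4.5 = 0.33, zinc 0.5/1.1 = 0.45.
- Per kcal (66 vs 80 kcal per 100 ml): phosphorus (26/66)/(56/80) = 0.56, or 44 % lower; calcium (47/66)/(100/80) = 0.57, or 43 % lower.
- At equal intake of 150 ml/kg/d, the minimum volume in the discharge criteria: phosphorus 1.5 × 26 = 39 vs 1.5 × 56 = 84 mg/kg/d; calcium 1.5 × 47 = 70.5 vs 1.5 × 100 = 150 mg/kg/d. This assumes that both arms take the same volume.

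**3. What baseline adjustment is worth**

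Let r be the within-arm correlation of the covariates, taken together, with the outcome. The documents give no value; 0.3 to 0.5 is assumed. Residual variance is multiplied by 1 − r², and the equivalent gain in sample size is 1/(1 − r²) − 1.

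- r = 0.3: 1 − 0.09 = 0.91; 1/0.91 − 1 = 10 %.
- r = 0.5: 1 − 0.25 = 0.75; 1/0.75 − 1 = 33 %.

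**4. How a shift in sampling age could matter**

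Suppose there are 148 infants per arm (the protocol's number completing the NICU part), no formula effect at any given age, and a difference in sampling age that moves one arm's mean by d standard deviations. The size of d is assumed; the documents give none. With δ = d/√(2/148) = d/0.116, a two-sided 5 % test rejects with probability 1 − Φ(1.96 − δ) + Φ(−1.96 − δ):

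| d (SD) | δ | Rejection rate |
|---|---|---|
| 0 | 0 | 5 % |
| 0.05 | 0.43 | 7 % |
| 0.10 | 0.86 | 14 % |
| 0.20 | 1.72 | 41 % |

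These rejections are false only as statements about a formula effect at a given age. As statements about status at discharge they are correct. With no age difference there is no distortion.

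**The case against.** The strongest reply is that this is one missing word. Phosphorus is still listed and still measured, a t test is valid in a randomised trial, and covariate detail is commonly left to a fuller plan. Much of this stands, and it limits the point. It does not remove the mismatch: the article itself gives both lists, and they differ. Nor does it remove the unevenness of a paragraph that states adjustment for some outcomes and a plain t test for these.

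Four stronger readings are tempting but not supported:

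- **That phosphorus is the mineral most affected by the formula.** Table 1 shows calcium reduced almost equally, with sodium, iron and selenium reduced further. Calcium also stays in the analysis. Growth in weight, length and head circumference bears on nutritional adequacy too, so the plasma markers are not the only evidence.
- **That the arms will be sampled at different ages.** The documents do not say so. It follows only if the hypothesis of a shorter stay holds. Discharge also requires a corrected gestational age of at least 34 weeks and a weight of at least 1500 g, and these criteria could limit or even reverse a difference with a lower-energy, lower-protein formula.
- **That the t test is confounded or invalid.** Age at discharge is a possible consequence of the formula, not a confounder. The unadjusted comparison validly estimates the total effect on status at discharge, which is how the endpoint is defined. A fixed-age comparison answers a different question.
- **That age at sampling should be a covariate.** It is post-randomisation and may be affected by the formula, so adjusting for it can bias the comparison.

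**Conclusion.** The point holds in a limited form and is minor. One of five listed plasma markers, phosphorus, has no stated analysis although it is collected weekly. This follows directly from the text and needs no assumption. The formula contrast that makes it relevant is 54 % per 100 ml, or 44 % per kcal.

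The unadjusted t tests are not an error. They are a less efficient choice than one available at almost no cost. The gain of 10 to 33 % in equivalent sample size rests wholly on assumed correlations of 0.3 to 0.5, and the trial is not sized on these markers.

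The link between sampling and discharge is a matter of interpretation. It would matter only if length of stay differs between arms, and the documents give no size for that.

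**What to change.** 1. Add phosphorus to the sentence that assigns an analysis to the plasma markers, so that it matches secondary endpoint 7.
2. Replace the t tests for all five markers by ANCOVA of the pre-discharge value on arm, gestational age and birth weight, and report each arm difference with a 95 % confidence interval. Do not include age at sampling as a covariate.
3. Add, as a supportive analysis, a mixed model of the weekly values with gestational age and birth weight as baseline covariates and postnatal age as the time scale. Report the arm difference at one postnatal age, fixed in advance, at which most infants are still in the NICU.

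The cost is wording and a little programming; every variable is already scheduled for collection. The one small downside lies in item 3. Discharged infants contribute no later weekly values, so the fixed-age contrast relies on values after discharge being missing at random. Choosing an age before most discharges keeps that reliance small.

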## Discussion

Extensively hydrolyzed milk protein formula can accelerate gastric emptying and gastrointestinal transit time, and promote gastrointestinal hormone secretion, and these mechanisms are conducive for the gastrointestinal tolerability of preterm children, thereby lowering the incidence of gastroesophageal reflux and feeding intolerance in preterm children, achieving full enteral nutrition as soon as possible and reducing the time of parenteral nutrition. In China, more and more medical organizations have started using extensively hydrolyzed milk protein formula to feed preterm children, but so far there is no clear conclusion on whether low-energy low-protein extensively hydrolyzed formula can meet the high nutritional needs of preterm children in the feeding period, and there is a lack of relevant studies and conclusions on whether feeding with extensively hydrolyzed milk protein formula in the early stage of life will affect the subsequent growth and development of preterm children. As the conflict between the high nutritional needs and low gastrointestinal tolerability of preterm children with a gestational age of less than 34 weeks is an unavoidable issue, we have designed this study protocol, aiming to increase a new and truly safe and effective enteral nutritional prescription. Our study observes the effect of extensively hydrolyzed milk formula on the feeding intolerance, enteral and parenteral nutrition, spontaneous fecal discharge and other complications in preterm children with a gestational age of less than 34 weeks during the NICU stay; it also is the first controlled clinical study with long-term observation of the growth and development of preterm children fed with such formula in the early stage of life. Our study time includes NICU stay and 3-month follow-up after discharge of preterm children. The results of this study will confirm that feeding preterm children with such formula during the NICU stay is safe and effective, and does not affect the normal growth and development of preterm children in the early stage of their lives.

## Trial status

We started the enrollment in November 2014 and the trial is expected to end in November 2017.

## Abbreviations

AAP: American Academy of Pediatrics
ALB: serum albumin
ALP: alkaline phosphatase
Ca: calcium
CH: congenital hypothyroidism
CMPA: cow’s milk protein allergy
CT: computed tomography
DB: direct bilirubin
DRI: direct rooming-in
EF: enteral feeding
EHF: extensively hydrolyzed formula
ESPGHAN: European Society for Pediatric Gastroenterology, Hepatology, and Nutrition
EUGR: extrauterine growth restriction
FI: feeding intolerance
FT_3_: free triiodothyronine
FT_4_: free thyroxine
GAS: gastrin
GER: gastroesophageal reflux
GRV: gastric residual volume
LCT: long-chain fatty acids
MCF: medium-chain triglycerides fat
MMC: migrating motor complex
MOT: motilin
MRI: magnetic resonance imaging
MV: mechanical ventilation
nCPAP: nasal continuous positive airway pressure
NEC: necrotising enterocolitis
NICU: Neonatal Intensive Care Unit
NNS: non-nutritive sucking
NRDS: newborn respiratory distress syndrome
P: phosphorus
P/E: protein-to-energy ratio
PICC: peripherally inserted central catheter
PN: parenteral nutrition
PNAC: parenteral nutrition-associated cholestasis
PS: pulmonary surfactant
PVC: percutaneous umbilical vein catheter
ROP: retinopathy
TB: total bilirubin
TBA: total bile acid
TP: total protein
TSH: thyroid-stimulating hormone
TT_3_: total triiodothyronine
TT_4_: total thyroxine
WHO: World Health Organization
